### Patient and public involvement

2.12

Patients and the public will not participate in the study’s design, recruitment, conduct, or reporting. Study results will be shared with participants via email.

## Discussion

3

In this prospective, randomized, open-label, controlled clinical trial, we will recruit 201 adult parturients undergoing cesarean delivery to assess the efficacy and safety of bilateral QL block with liposomal bupivacaine for post-cesarean analgesia. This study will be implemented in accordance with the Consolidated Standards of Reporting Trials guidelines and address three critical clinical questions regarding the proposed postoperative analgesic strategy. First, whether it fulfills fundamental analgesic requirements. Second, whether it independently achieves contemporary standards for comprehensive pain management. And, whether it confers clinically significant co-benefits beyond analgesia. The primary outcome is postoperative pain intensity, evaluated using the VAS pain score during standardized movement at 12, 24, 48, and 72 h post-surgery. Secondary outcomes include quality of recovery (QoR-15 scores), VAS scores at rest, need for rescue analgesia, postoperative anxiety regarding a hypothetical repeat cesarean section, subjective sleep quality, maximum walking duration, patient satisfaction with analgesia, postoperative nausea and vomiting, opioid consumption, and hospital length of stay.

The three-arm design of this trial was structured to address two key clinical questions regarding post-cesarean analgesia. First, by comparing bilateral QL block with liposomal bupivacaine to standard intravenous analgesia alone, the study aims to evaluate whether a single-injection, long-acting regional technique can provide superior pain control and reduce reliance on systemic opioids. Second, the inclusion of a group receiving QL block with ropivacaine combined with intravenous analgesia allows for a direct comparison between liposomal and conventional local anesthetics in terms of both analgesic efficacy and opioid-sparing potential. This design facilitates a comprehensive assessment of the relative benefits of QL block strategies, not only in improving postoperative pain outcomes but also in minimizing opioid-related adverse effects.

Liposomal bupivacaine, an extended-release formulation, prolongs local anesthetic effects for at least 72 h by controlling the release of encapsulated bupivacaine (15). Its clinical efficacy and safety have been well-documented in multiple surgical settings, demonstrating superior pain control and opioid-sparing effects (24, 25). A study on post-hemorrhoidectomy pain found that liposomal bupivacaine, when administered via local infiltration anesthesia, extended analgesia to an average of 14.3 h before additional analgesia was required, compared to 1.2 h in the control group (26). When administered via TAP blocks, this formulation achieved a maximum complete analgesia duration of 15 h, significantly exceeding conventional local anesthetics, furthermore, those patients exhibited superior recovery metrics during the 72-h postoperative period (27). Notably, its administration via bilateral TAP nerve blocks has significantly reduced opioid consumption following cesarean delivery (28). However, relevant clinical data on the application of liposomal bupivacaine in bilateral QL blocks are lacking. A critical safety consideration is the potential transfer of bupivacaine into breast milk; studies indicate that the relative neonatal dosage remains below 1%, well within safe limits (14). These findings reinforce the potential of liposomal bupivacaine as an effective and safe component of postoperative pain management, particularly in opioid-reduction strategies.

Advancements in regional anesthesia techniques continue to refine multimodal analgesia strategies. Evidence suggests that QL blocks provide superior and prolonged analgesia compared to TAP blocks in lower abdominal surgeries, including cesarean sections (18). Cadaveric studies demonstrate extensive dye dispersion beyond the transverse processes and nerve roots, further supporting the hypothesis that QL blocks may provide broader and longer-lasting analgesic effects (20). MRI studies in volunteers have also shown that contrast injected via the QL block approach achieves extensive paravertebral spread, reinforcing its potential superiority over TAP blocks (29). Given these findings, the bilateral QL block was selected for this study to optimize postoperative pain control. This study aims to evaluate whether bilateral QL blocks with liposomal bupivacaine can optimize postoperative pain management while reducing analgesic consumption and adverse events in cesarean delivery patients. Methodologically, the investigation will first compare this intervention with standard PCIA to determine if it offers additional benefits in postoperative pain control and reduces the incidence of adverse reactions. Subsequently, the liposomal bupivacaine-based bilateral QL block strategy will be further contrasted with the R-P group (a multimodal analgesia regimen combining regional techniques and pharmacologic agents) to assess whether it achieves comparable clinical benefits to established multimodal protocols. We hypothesize that bilateral QL nerve blocks with liposomal bupivacaine will provide superior postoperative analgesia, reduce opioid consumption, and offer improved safety and practicality. If validated, this approach could significantly optimize post-cesarean recovery protocols and mitigate analgesic-related adverse effects.

Beyond its clinical impact, this study also aims to explore the potential societal implications of effective postoperative pain management. By mitigating postpartum pain and anxiety, improved analgesic strategies may positively influence fertility intentions and maternal wellbeing (3). Addressing postpartum pain through optimized regional anesthesia techniques may help alleviate childbirth-related fears, contributing to a more positive childbirth experience and possibly influencing broader public health trends related to reproductive choices (30).

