**Methods:**

This single-center, open-label, randomized controlled trial will enroll 201 adult parturients undergoing lower segment transverse cesarean section. Participants will be randomized in a 1:1:1 ratio into three groups (*n* = 67 each): Group LB will receive bilateral quadratus lumborum block with liposomal bupivacaine under ultrasound guidance. Group R-P will receive bilateral quadratus lumborum block with ropivacaine in combination with patient-controlled intravenous analgesia. Group P will receive standard patient-controlled intravenous analgesia without regional nerve block. The primary outcome is postoperative pain intensity, assessed using the Visual Analogue Scale during standardized movement at 12, 24, 48, and 72 h postoperatively. A generalized estimating equation model will be used to assess the overall effect of treatment group on pain scores over time. Secondary outcomes include patient-reported Quality of Recovery-15 scores at 24 and 48 h postoperatively; Visual Analogue Scale for pain at rest, measured at 12, 24, 48, and 72 h postoperatively; need for rescue analgesia; postoperative anxiety (assessed by Visual Analogue Scale at 72 h); subjective sleep quality; maximum walking duration; patient satisfaction with analgesia; incidence of nausea and vomiting; postoperative sufentanil consumption and length of hospital stay. Safety outcomes include allergic reactions, wound infection, lightheadedness, headache, circumoral numbness, tongue paresthesia, drowsiness, irritability, blood pressure fluctuations (hypotension, hypertension), respiratory depression (hypoventilation), and cardiac events (bradycardia, tachycardia, arrhythmia, cardiac arrest). Data will be analyzed using a modified intention-to-treat approach.

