### Anaesthetic and study interventions

2.8

All patients fast for at least 8 h and abstain from water for 4 h preoperatively. In the operating room, after establishing a peripheral intravenous channel, they inhale oxygen at 5 L/min via mask, with continuous monitoring of vital signs: non-invasive blood pressure, percutaneous arterial oxygen saturation (SpO_2_), heart rate, and respiratory rate. Preoperatively, all parturients will receive combined spinal-epidural anesthesia. The parturient will be placed in the lateral decubitus position. Following standard aseptic skin preparation and draping with a sterile aperture sheet, subarachnoid blockade will be performed. At the L2/3 or L3/4 interspace, 10–14 mg of 0.5% ropivacaine will be administered intrathecally to achieve rapid onset of surgical anesthesia. An epidural catheter will then be inserted for subsequent intraoperative supplementation if required. In case of inadequate block height or duration, incremental boluses of 2% lidocaine (3-5 mL) or 1% ropivacaine (5 mL) will be administered through the epidural catheter, with careful titration based on the patient’s response and hemodynamic status. Continuous monitoring will be maintained for signs of local anesthetic systemic toxicity, such as tinnitus, perioral numbness, or altered mental status. For parturients with extreme body habitus or height (affecting drug distribution and blockade levels), local anesthetic dosing will be precisely calibrated based on individual anthropometric measurements to optimize analgesic efficacy and safety. Dosing will be precisely calibrated in accordance with each patient’s anthropomorphic measurements to ensure optimal analgesic outcomes. Upon verification of both the requisite analgesic level (at least T6) and the efficacy of the blockade, the cesarean section will be initiated. Supine hypotensive syndrome and total spinal anesthesia are medical emergencies requiring immediate treatment, so, intensive monitoring during the surgical procedure and maintaining hemodynamic stability with the utilization of vasoactive medications as needed to support vital sign parameters are essential. All patients will receive postoperative analgesic regimens as dictated by the sealed-envelope protocol. This information is exclusively known to the anesthesiologist administering the anesthesia, with all other individuals involved remaining blinded to the details. Participants in group LB will receive bilateral QL nerve block [posterior QL block (20)] utilizing liposomal bupivacaine injection under ultrasound guidance (Liposomal bupivacaine injection, 133 mg per 20 mL on each side); participants enrolled in group R-P will receive bilateral QL nerve block utilizing ropivacaine injection under ultrasound guidance (Ropivacaine injection, 20 mL of 0.375% ropivacaine on each side), in conjunction with a PCIA; and participants enrolled in group P will be managed with standard PCIA, without supplementary nerve block interventions. In the preparation of PCIA pumps, each total volume is standardized at 100 mL, and the formulation includes sufentanil and 8 mg of ondansetron. The total amount of sufentanil is calculated based on a dosage of 2 μg per kilogram of body weight. The background infusion rate is set within the range of 0.04 μg/kg/h. The PCIA protocol is set with a 0.04 μg/kg bolus dose and a 15-min lockout interval to ensure safety.

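### LB v R-P compares two regimens, not two local anesthetics: only R-P also has the PCIA pump, so the direct drug comparison named in the Discussion is not identified

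*Protocol article*

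**What the plan says.** The second paragraph of the Discussion gives the three-arm design two purposes. The second is that the ropivacaine group "allows for a direct comparison between liposomal and conventional local anesthetics in terms of both analgesic efficacy and opioid-sparing potential".

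The abstract's Methods define the arms:
- LB: "Group LB will receive bilateral quadratus lumborum block with liposomal bupivacaine under ultrasound guidance".
- R-P: "Group R-P will receive bilateral quadratus lumborum block with ropivacaine in combination with patient-controlled intravenous analgesia".
- P: "Group P will receive standard patient-controlled intravenous analgesia without regional nerve block".

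Section 2.8 agrees. It gives R-P its block "in conjunction with a PCIA; and participants enrolled in group P will be managed with standard PCIA", and it describes LB by its block alone. Of the pump it says that "the formulation includes sufentanil and 8 mg of ondansetron", with a background infusion of 0.04 μg/kg/h from a total of 2 μg/kg. The intervention rows of Table 1 likewise attach PCIA to ropivacaine and to the third arm, but not to liposomal bupivacaine. Section 2.5 counts PCIA sufentanil as well as rescue oxycodone in 0–72 h opioid use.

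Later in the Discussion, the R-P comparator is called "a multimodal analgesia regimen combining regional techniques and pharmacologic agents", and the question becomes whether the LB strategy gives comparable benefit. The abstract's Discussion also uses regimen terms. Limitations (section 3.1) does not mention that the two block arms differ in PCIA.

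**The concern.** LB and R-P differ in two components at once: the drug in the block, and the presence of an opioid and antiemetic pump. The Discussion attributes the contrast to the first component alone, for both pain and opioid sparing.

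The pump pushes the two outcomes in opposite directions. If it relieves pain, it works against LB on VAS. On opioid consumption it works in favour of LB, because only the R-P total includes pump sufentanil. A reader told that this is a drug comparison could take equal pain scores as equal drugs, and lower opioid use as a property of the liposomal formulation. Neither inference would follow.

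**Working it through.** **1. What the three arms identify.** Let b be mean pain without study analgesia, and let L, R and Q be the pain reductions from the liposomal block, the ropivacaine block and the pump. Take the effects as additive, which is the assumption most favourable to the plan.

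- Arm means: LB = b − L; R-P = b − R − Q; P = b − Q.
- Advantage of R-P over P: R.
- Advantage of LB over P: L − Q.
- Advantage of LB over R-P: L − R − Q.

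The drug contrast is D = L − R. To obtain it from a weighted sum of the three means, L needs weight −1 on LB, R needs weight +1 on R-P, and cancelling b then forces weight 0 on P. That sum is L − R − Q, so Q remains. More patients or another model for the same three arms would not remove it.

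**2. Size of the pain distortion.** The plan gives no figure for this contrast or for Q, so there is none to reproduce. Inputs from section 2.10 are SD 1.55, difference 1.40, ICC 0.53, four measurements, pairwise alpha 0.05/3, and 67 per arm less 10% dropout, which is about 60. As a check on SD and difference, the single-measurement calculation 2 × (1.960 + 0.842)² × 1.55² / 1.40² = 19.2 rounds up to the plan's 20 per group.

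- SE of the difference in four-visit means = √[2 × 1.55² × (1 + 3 × 0.53) / (4 × 60)] = 0.228.
- Two-sided critical z at 0.05/3 = 2.394, so the smallest significant difference is 2.394 × 0.2277 = 0.545.
- P(LB significantly better) = Φ[(D − mean Q − 0.545) / 0.228].

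Q is assumed over 0 to 1.4 points. How long it lasts also matters: at the background rate alone the reservoir lasts at most 2 / 0.04 = 50 h, and no refill is described. The last two columns set Q to zero at 72 h, so that mean Q is three quarters of the assumed value.

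| True D | Assumed Q | Net, Q at all visits | P(LB better) | Net, Q absent at 72 h | P(LB better) |
|---|---|---|---|---|---|
| 1.40 | 0 | 1.40 | 1.00 | 1.40 | 1.00 |
| 1.40 | 0.7 | 0.70 | 0.75 | 0.875 | 0.93 |
| 1.40 | 1.4 | 0.00 | 0.01 | 0.35 | 0.20 |

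Conversely, with equal drugs (D = 0) and Q = 1.0, LB is declared significantly worse with probability 0.98 if Q acts at all visits, or 0.82 if it is absent at 72 h.

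**3. Opioid use.** The background infusion alone delivers 0.04 × 24 = 0.96 μg/kg of sufentanil in the first 24 h in R-P. LB has no pump, so its opioid total can come only from rescue oxycodone. This part of the difference would appear even if the two local anesthetics were identical.

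**4. Nausea and vomiting.** The pump carries both sufentanil and ondansetron, and only one of the two block arms has it. The contrast mixes both pump components with any effect of the block drug.

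**The case against.** The strongest reply is that this is one sentence of the Discussion. The aim, primary outcome, sample size and analysis sections compare three randomized groups and make no claim about one drug against the other. The sentence itself mentions that the ropivacaine block is combined with intravenous analgesia, and the later paragraph and the abstract already speak of strategies or regimens. A pump-free LB arm is also deliberate, because the trial asks whether a single injection can stand on its own. All of this stands. It makes the correction easy, but it does not make the sentence true: the sentence states the purpose of the R-P arm and expressly includes opioid sparing, where the allocation effect is plainest.

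A reader might go further and infer that LB v R-P is uninformative, or that no drug-level inference is possible at all. The documents do not support that. The contrast is a valid randomized comparison of two regimens. If Q is not negative, a significant LB advantage on pain implies D > Q ≥ 0, so it supports a drug advantage conservatively. This matters because superiority is the stated hypothesis. The bound does not rescue opioid sparing.

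A reader might also take the extreme probabilities as forecasts. They are not. Q is assumed, its upper end equals the whole clinically important difference on top of a working block, rescue analgesia is available in every arm, and the reservoir limit makes a constant effect through 72 h doubtful. Nor do the documents show that results will be misreported: the Conclusion does not rank the two local anesthetics.

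**Conclusion.** The concern holds for the claim of a direct drug comparison. LB v R-P estimates the drug difference minus the pump effect, and the drug effect alone is not identified by any combination of the three arms.

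- **Pain:** a null or unfavourable LB result cannot be read as a statement about the two drugs. A favourable one can, on the stated assumption that PCIA does not increase pain.
- **Opioid use:** the difference is partly set by allocation.
- **Nausea and vomiting:** the contrast is confounded by the pump contents.

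The non-identification rests only on the arm definitions. The documents never say in words that LB has no pump, and Figure 1 is not shown, but the arm descriptions and Table 1 leave no other natural reading. The size of the pain distortion is uncertain. For a true drug advantage of 1.40, the probability of detection is about 1.00 with no pump effect, 0.75 to 0.93 at an assumed pump effect of 0.7, and 0.01 to 0.20 at 1.4, depending on whether that effect lasts to 72 h. The comparison of regimens is unaffected.

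**What to change.** 1. In the Discussion paragraph on the three-arm design, describe LB v R-P as a comparison of two regimens, liposomal bupivacaine block alone against ropivacaine block plus PCIA. This brings it into line with the later Discussion paragraph and the abstract.
2. State that this contrast will support no conclusion about opioid sparing or adverse effects of the drugs themselves, and no drug-level conclusion of equivalence or inferiority on pain. If a pain advantage for LB is to be read at drug level, state the assumption that PCIA does not increase pain.
3. Add the difference in PCIA between the two block arms to Limitations (section 3.1).

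The cost is wording only. Arms, doses, sample size and analysis stay as they are, and the sponsor gives up a claim that the design cannot support.

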### Secondary outcomes

2.5

Secondary outcomes will include patient self-assessment of the Quality of Recovery-15 (QoR-15) scale at 24 and 48 h postoperatively, as well as Visual Analog Scale (VAS) pain scores at rest, recorded at 12, 24, 48, and 72 h post-surgery. Additionally, the number of postoperative acute analgesic requests will be documented. Postoperative anxiety regarding the hypothetical repeat cesarean section will be assessed at 72 h post-surgery using the VAS score (scores range from 0 to 10, with 0 indicating the best and 10 indicating the worst, named VAS anxiety score) (19). Subjective sleep quality will be evaluated for 24, 48, and 72 h post-surgery using the Numerical Rating Scale (NRS) (scores range from 0 to 10, with 0 indicating the worst and 10 indicating the best sleep quality). The maximum walking duration, defined as the longest duration a patient can walk after surgery, will be measured at 24, 48, and 72 h post-surgery. Patient satisfaction with analgesic management will be assessed at 24, 48, and 72 h post-surgery using the NRS (scores range from 0 to 10, with 0 indicating the worst and 10 indicating the best). Postoperative opioid use (including sufentanil via PCIA and any rescue oxycodone) will be recorded over the 0–72 h period. For comparability, all opioid doses will be converted to intravenous morphine milligram equivalents (MME) using standard equianalgesic conversion factors. Both the raw consumption of sufentanil and oxycodone as well as the total MME will be reported. Furthermore, the incidence of nausea and vomiting and length of hospital stay will be recorded.

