### Safety outcomes

2.6

Safety outcomes will assess postoperative adverse reactions including, allergy, wound infection, lightheadedness, headache, circumoral numbness, tongue paresthesia, drowsiness, irritability, hypotension, hypertension, hypoventilation, bradycardia, tachycardia, arrhythmia, and cardiac arrest.

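### The listed safety outcomes have no item for leg weakness or numbness, falls or block-site complications, although the block is chosen for its wide spread and the drug is said to act for at least 72 h

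*Protocol article*

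**What the plan says.** Section 2.6 of the protocol article sets the safety outcomes: "Safety outcomes will assess postoperative adverse reactions including, allergy, wound infection, lightheadedness", then "headache, circumoral numbness, tongue paresthesia, drowsiness, irritability, hypotension, hypertension, hypoventilation, bradycardia, tachycardia, arrhythmia, and cardiac arrest". That makes 15 items. The adverse-event rows of Table 1 (section 2.9) carry the same 15, each at 0, 12, 24, 48 and 72 h. Nausea and vomiting are recorded separately as a secondary outcome.

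Section 3 (Discussion) gives the anatomical case for the block: "Cadaveric studies demonstrate extensive dye dispersion beyond the transverse processes and nerve roots", and volunteer imaging in which "contrast injected via the QL block approach achieves extensive paravertebral spread". It says that the liposomal drug "prolongs local anesthetic effects for at least 72 h", and that clinical data on its use in bilateral quadratus lumborum blocks are lacking. The same section makes safety an aim. It asks whether the LB strategy lowers adverse reactions compared with intravenous patient-controlled analgesia (PCIA), and hypothesises that it will be safer. The Conclusion again promises evidence on safety.

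Three other provisions bear on the point. Section 2.8 gives combined spinal-epidural anesthesia to every patient. Section 2.9 requires all serious adverse events to be reported, related or not. Section 2.5 includes a mobility outcome at 24, 48 and 72 h: "The maximum walking duration, defined as the longest duration a patient can walk after surgery".

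**The concern.** The plan uses the spread and duration of the block to predict benefit but schedules no item for the regional effects that the same spread and duration might cause. Several listed items are effects one would look for with an opioid pump, such as drowsiness and hypoventilation. No item is a local effect of the needle or a regional effect of the injectate.

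What is at stake is the safety comparison of LB with P, which the Discussion makes one of the trial's purposes. If non-serious weakness, numbness, falls or hematoma are not asked about, a lower total of adverse reactions in LB could partly reflect what was counted. The primary outcome and its analysis are not affected.

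**Working it through.** No figure in the plan is in dispute. The check is a comparison of texts, followed by a scale calculation on assumed rates.

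**Step 1: sort the 15 items of section 2.6.** The grouping is mine, and some items could sit in more than one group.

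| Type of effect | Items listed |
|---|---|
| Possible local anesthetic toxicity | circumoral numbness, tongue paresthesia, arrhythmia, cardiac arrest (drowsiness and irritability may also belong here) |
| Opioid-type | drowsiness, hypoventilation, lightheadedness |
| Hemodynamic | hypotension, hypertension, bradycardia, tachycardia |
| General | allergy, wound infection, headache |
| Regional or block-site | none |

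The toxicity row is supported by section 2.8, which refers to "signs of local anesthetic systemic toxicity, such as tinnitus, perioral numbness, or altered mental status". Wound infection is not defined as covering the injection site. Table 1 adds no adverse-event row beyond the 15.

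**Step 2: ask in which arms each missing effect can occur (section 2.8).**

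| Missing item | LB | R-P | P |
|---|---|---|---|
| Leg weakness or numbness | yes | yes | yes, after combined spinal-epidural anesthesia |
| Fall | yes | yes | yes, for the same reason, and P also receives an opioid |
| Block-site hematoma or injury | yes | yes | no, as there is no block |

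Only the last row is exclusive to the block arms. For the first two, the question is whether the block adds to a background rate, which can be answered only if all arms are asked.

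**Step 3: see what other provisions pick up.** Serious events reach the data monitoring committee through section 2.9. A non-serious event of these types has no scheduled item. Walking duration (section 2.5) would register weakness indirectly, as a shorter walk, but it is not a count of harm.

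**Step 4: scale.** Inputs: 67 patients per group (section 2.10), so 2 × 67 = 134 in the two block arms. The event rate p is not in the documents; 1% to 5% is an assumption. The chance of at least one case is 1 − (1 − p)^n.

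| Assumed p | n = 67 (LB alone) | n = 134 (LB and R-P) |
|---|---|---|
| 1% | 1 − 0.99^67 = 49% | 1 − 0.99^134 = 74% |
| 2% | 1 − 0.98^67 = 74% | 1 − 0.98^134 = 93% |
| 3% | 1 − 0.97^67 = 87% | 1 − 0.97^134 = 98% |
| 5% | 1 − 0.95^67 = 97% | 1 − 0.95^134 = 99.9% |

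If the items were collected and no case seen, the one-sided 95% upper bound on the rate would be 1 − 0.05^(1/n): 4.4% for n = 67 and 2.2% for n = 134. If they are not collected, no bound can be stated.

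**The case against.** The strongest case on the other side has five parts.

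- **The list is not blind to harms of the block.** Circumoral numbness and tongue paresthesia are asked at every visit from 0 to 72 h and would count mainly against the arms given extra local anesthetic. This stands. A reader might infer that the harms only the block arms can have go uncounted altogether; the documents do not support that, since toxicity signs are listed and serious events are reported regardless of cause.
- **Leg weakness and falls are not specific to the block.** This stands too, and is why the items should be asked in all arms.
- **The link from spread to leg symptoms is not in the documents.** The Discussion cites dye and contrast spread in support of analgesia, and reports no motor effect. That local anesthetic near nerve roots can weaken or numb the legs is a general assumption, and its frequency with this approach is unknown here. It is still reason enough to ask, given that the article calls data on this use lacking.
- **The article condenses a fuller protocol, and section 2.6 introduces its list as non-exhaustive.** The case report form may hold more. Against this, Table 1 is itemised down to tongue paresthesia and matches section 2.6 exactly.
- **Walking duration already captures mobility.** It does, as net function: if weakness shortens walking, that counts against the block. A reader might infer that the outcome is invalid because its cause is not recorded. It is not. The randomized comparison holds, and only its explanation is left open.

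**Conclusion.** The point holds in a limited form. The itemised safety set omits leg weakness or numbness, falls and block-site complications, while the article relies on wide spread, claims an effect of at least 72 h and hypothesises better safety for LB. Followed as written, non-serious regional effects have no scheduled item while opioid-type effects do, so the adverse-reaction comparison of LB with P is incomplete in the direction that favours LB.

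The size of the effect cannot be established from the documents. The probabilities above rest on assumed rates. They show that the trial would probably see at least one case in LB at rates of about 2% or more (74% at 2%) if it asked. They do not show that such cases will occur, or that the safety conclusion would change. The finding also assumes that the full case report form has no further items of this kind.

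**What to change.** Add to section 2.6 and to the adverse-event rows of Table 1, in all arms and at the visits already scheduled:

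- new leg weakness or numbness (yes/no);
- any fall (yes/no);
- block-site hematoma or new focal nerve deficit (yes/no; the hematoma part does not apply in P).

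Report these by arm beside the other safety outcomes, under the rule of section 2.11 that patients are analysed as originally allocated. A separate grouping by treatment received would conflict with that rule and is not needed here.

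Recording whether walking was limited by pain, leg weakness or something else is an optional aid to interpreting the walking outcome. If the full case report form already holds these items, it is enough to list them in section 2.6 and Table 1.

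The cost is a few more fields, completed by the nurses who already make the postoperative assessments. No visit, treatment or sample size changes.
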